**Fig. 4 Fig4:**
[figure not shown]
Screen shots of the AMPED mobile application.

##### Physical activity feedback for teachers

During the second workshop, teachers will be provided with private, individualized information regarding their students’ MVPA levels during lessons at baseline (as measured via accelerometry). In their action plan near the end of the workshop, teachers will be asked to set a goal for MVPA during lessons in the upcoming term. In the first four weeks following the workshop, a research assistant will visit each teacher’s class and fit students with accelerometers for one lesson. These data will be processed and mentors will provide teachers with feedback regarding student MVPA levels during their individual mentor meetings later in the term.

#### Booster intervention

Five months after the end of the intervention, mentors will meet with experimental group teachers for a half-day face-to-face workshop in each school. The purpose of this meeting is to reflect on the core principles of (i) lesson planning and delivery and (ii) motivational support from the first two workshops. Teachers will be encouraged to reflect and discuss their attempts to improve their practice from the previous year. Each teacher will be asked to create an action plan for the upcoming term and use the website or mobile app to reflect on his or her implementation by the middle of the term. In the final weeks of the term, each school will be asked to hold a final group mentoring meeting. A member of the school’s PE staff will facilitate this meeting; project mentors will not be present. Teachers will be able to access the project website and the mobile app throughout the rest of the study, including the maintenance phase assessment.

Teachers in the control condition will not receive training during the main RCT, but will be offered this opportunity in the period following the trial.

#### Compensation

All teachers who complete AMPED training will receive 23 registered hours of NSW Board of Studies, Teaching and Educational Standards teacher professional learning credits at no charge; NSW teachers must complete 50 hours of registered teacher professional learning every five years to maintain their accreditation. Teachers will also keep their touchscreen tablet computer that will be provided to facilitate interaction with project website. Finally, at each data collection time point, teachers will receive a $50 gift card to compensate them for time spent organizing student consent and facilitating data collection scheduling, a task that is beyond their usual teacher duties. All of this compensation will be provided equally to teachers in the intervention and wait-list control schools.

### Fidelity

Three lessons from each class in the experimental and control conditions will be video- and audio-recorded during baseline, post-intervention, and maintenance phase assessment periods. The video camera will be located at an angle that allows the entire lesson to be recorded. Audio recordings of the lesson will be captured using a wireless microphone. Trained, blinded observers will rate a random sample of 10 % recordings (approximately 60 of 600 lessons) to assess fidelity of implementation. Intervention fidelity will be confirmed if, compared with controls, the intervention condition’s lessons during the post-intervention and maintenance phases show greater implementation of teaching strategies taught during the intervention, including (i) lesson planning/delivery strategies designed to maximize opportunities for physical activity during lessons and (ii) strategies designed to support student needs satisfaction and foster autonomous motivation. See Table 2 for a full listing of AMPED strategies and Additional file 1: Appendix B for details on the rating protocol.

### Outcomes

Trained research assistants will collect all outcome data, including behavioral outcomes, psychological outcomes and educational outcomes. To ensure consistency and enhance data quality, these researchers will follow standard operating procedures (as outlined in a protocol manual) before, during, and after all data collection sessions. Questionnaire data will be collected in regularly scheduled classroom lessons, supervised by two research assistants who will follow a ‘read-aloud’ protocol for questionnaire instructions and items.

#### Primary outcome

MVPA during PE lessons-ActiGraph accelerometers (ActiGraph, LLC, Fort Walton Beach, FL) will be used to measure PA during three PE lessons at each time point (baseline, post-intervention, and maintenance). Accelerometer models will include GT1M, GT3X, and GT3X+, which have been shown to have extremely high levels of agreement both in terms of counts per minute and MVPA estimates [50]. Accelerometers will be attached using cotton, elastic belts to the students’ hip at the top of the right iliac crest.

Lesson start and end times will be signified by the school bell and will be recorded by researchers on site. These times will be used to process accelerometer data and determine PA that occurs during each PE lesson.

Prior to data collection, accelerometers will be initialized and set to record data using a 1 sec epoch or 60hz (for GT3X+). Data will be processed using Actilife software (Version 6, ActiGraph, LLC, Fort Walton Beach, FL), with 1 sec vertical axis data used to classify activity intensity according to Evenson and colleagues’ [51] cutpoints, which have been shown to be the most accurate in this age group [52]: moderate-to-vigorous activity >2296 counts per minute. To convert the cutpoint definition for 1 s epochs, the cut-point will be divide by 60.

#### Secondary outcomes

##### Behavioral outcomes

Sedentary behavior and light, moderate and vigorous physical activity during PE lessons-In addition to MVPA during PE lessons, accelerometer data will be used to examine the amount of lesson time spent in sedentary behavior and light, moderate and vigorous physical activity: vigorous activity (>4012 counts per minute), moderate activity (2296–4011 counts per minute) and light intensity activity (101 – 2295 counts per minute). Sedentary behavior will be classified as ≤100 counts per minute.

Student participation rate in PE lessons-Research assistants will record the total number of students at each lesson, the number of students at each lesson that are not participating and the number of students absent from each lesson. These data will be used to calculate the proportion of students’ participating in each lesson.

Physical activity and sedentary behavior during leisure time (i.e., outside school)-Students will be instructed to wear their accelerometer for five weekdays and two weekend days at each time point (baseline, post-intervention, and maintenance). Accelerometer data processing procedures (e.g., activity intensity classification) will be consistent with those described for PE lessons. Periods of non-wear time will be defined as 30 minutes or more of consecutive ‘0’ counts and will be removed from the dataset. This non-wear criterion was chosen because research with adolescents indicates that 30-minute bouts of sedentary behavior (≤100 counts per minute) are extremely rare [53]. To be included in the analyses, the student will need to provide valid data for at least three days in total, including at least two weekdays. Valid days will be defined as days with ≥ 8 h of wear time. These criteria have been chosen because: (i) compared to more stringent criteria, they are likely to minimize missing data, which is important for maintaining population representativeness in this repeated-measures group randomized trial [54, 55]; and (ii) they are relatively consistent with other accelerometer studies in adolescents [56]. To ensure increased compliance with this protocol we will: (i) deliver thorough, clear, and standardized initial instructions during a classroom lesson; (ii) send an SMS text message to students each morning reminding them to put the accelerometer on; and (iii) send an SMS text message prior to the day of accelerometer collection to ask teachers to give a verbal reminder to students regarding wearing and return. Leisure time MVPA will also be measured subjectively using an adaptation of two versions of the Health Behavior in School-Aged Children questionnaire [57, 58].

##### Psychological outcomes

Students’ physical self-concept-Aspects of students’ global and physical self-concept will be measured using 21 items from the Physical Self Inventory. This scale includes items to measure: (i) global self-worth; (ii) physical self-worth; (iii) physical appearance; (iv) sport competence; (v) physical condition; and (vi) physical strength [59].

Students’ subjective well-being-The Positive and Negative Affect Scale for Children will be used to measure subjective well-being. This scale has produced reliable and valid scores in youth samples [60].

##### Educational outcomes

Student engagement in academic lessons-Students’ self-reported engagement during mathematics lessons will be measured using a questionnaire that was originally designed to measure school engagement [61], and later adapted to a mathematics setting [62]. The questionnaire aims to assess students’ cognitive, behavioral and affective engagement. At each time point, students will be asked during a mathematics lesson to report on their typical engagement with mathematics (e.g., “I like maths lessons”). On a different day, students’ will also report on their level of engagement during that specific lesson (e.g., “Today, I liked the maths lesson”).

On-task behavior during academic lessons—We will also video record students’ mathematics lessons. These recordings will be analyzed using a momentary time sampling procedure to determine students on-task behavior. This procedure has been successfully implemented in investigations conducted by others [7]. Analysis of observations will take place from data gathered at baseline and post-intervention. Within lessons, students will be chosen at random and observed in intervals for the duration of the lesson. Students will be observed and categorized as being either on or off task. Additionally, on-task behavior will be further coded as actively engaged or passively engaged. Intra- and inter-observer reliability will be established before the assessment period.

Student academic performance – will be measured by collecting National Assessment Program Literacy and Numeracy (NAPLAN) scores from records held by the NSW Department of Education.

#### Motivational mediators

Students’ perceptions of teachers’ needs supportive and controlling behaviors-Students’ perceptions of their PE teacher’s involvement (i.e., relatedness support), structure (i.e., competence support) and autonomy support will be measured using 12 items from the Teacher as Social Context Questionnaire [63]. Student perceptions of controlling behavior will be measured using the intimidation and conditional regard subscales of the Controlling Interpersonal Style Scale (adapted to suit the PE context) [64].

Psychological Needs Satisfaction during PE lessons-Autonomy [65], competence [66], and relatedness [67] need satisfaction scales. These measures have produced strong reliability and validity evidence in adolescent samples [19].

Autonomous motivation, controlled motivation and amotivation towards PE-Perceived Locus of Causality Questionnaire [68]. Scores derived from this questionnaire have shown good reliability and validity in multiple adolescent samples [69].

Autonomous motivation, controlled motivation and amotivation towards leisure-time PA-Behavioral Regulation in Exercise Questionnaire-2 [70]. This measure has produced reliable and valid scores in studies involving adolescent samples. [71].

#### Demographic information

Students will report their country of birth and language spoken at home. Using categories based on the Australian Bureau of Statistics’ Standard Classification of Languages [72], we will use language data to categorize students into one of seven ethnic backgrounds (English, European, Middle Eastern, Asian, African, South Pacific, or ‘other’). Students will also indicate if they are of Indigenous origin (i.e., Australian Aboriginal or Torres Straight Islander). We will measure the socioeconomic status of each participant’s family using the Family Affluence Scale [73].

Research assistants will measure students’ height to the nearest 0.1 cm using a portable stadiometer (Surgical and Medical Products No. 26SM, Medtone Education Supplies, Melbourne, Australia). They will also measure students’ weight to the nearest 0.1 kg using digital scales (UC-321, A&D Company LTD, Tokyo, Japan). These data will be used to calculate each student’s body mass index (BMI) and BMI Z-score [74].

#### Covariates-related to MVPA during PE lessons

Temperature at the start of the PE lesson will be measured using an electronic thermometer (HC520 Thermometer, CS Raffles Tech Inc., Singapore). The type of activity being taught during the lesson will also be recorded and categorized as follows: (i) invasion games; (ii) striking and fielding games; (iii) target games; (iv) net/wall games; (v) fitness activities; (vi) artistic activities; (vii) athletics; (viii) other; and (ix) mix of activities. Finally, at some lessons students will arrive wearing an accelerometer that they have been provided in order to measure their daily MVPA (7-day wear period). For other lessons, students will be fitted with an accelerometer when they arrive at the lesson. The timing of this fitting (i.e., do they arrive at the lesson wearing an accelerometer or not?) will be recorded for each student at each lesson.

### Statistical analysis

Between-arm differences in changes on the primary and secondary outcomes will be analyzed using generalized linear mixed models according to intention-to-treat and per-protocol principles. Specifically, intention to treat analyses will involve analysis of outcomes collected from all students who completed baseline assessment, regardless of whether or not they complete post-intervention or maintenance phase assessments. Between-arm differences in changes on the primary and secondary outcomes will be assessed by including an indicator variable for group allocation (arm), a variable representing time (baseline, post-intervention, and/or maintenance) and their interaction.

For the primary outcome (MVPA during lessons), student data will be gathered from between one and three lessons per student at each of the time points (baseline, post-intervention and maintenance). The repeated measure will be modeled as a random intercept effect. Lesson will also be modeled as a random intercept effect. Analyses will also be adjusted for class and teacher clustering-each teacher will be given a case ID. In instances where teachers ‘team-taught’ (i.e., two teachers within a single lesson), we will create a new case ID that is unique to that combination of teachers. In some instances students will be taught by different teachers within a time point (i.e., from lesson to lesson) or across time points (e.g., from baseline to post-intervention). We will account for this data structure by specifying cross-classified random effects models. Possible school-level residual clustering will be explored and included in the models, if appropriate. In sum, we will include four random intercept effects: (i) lesson; (ii) student; (iii) teacher; and (iv) class. We will consider a fifth random intercept effect for school, if preliminary analyses suggest clustering of MVPA during lessons at the school level.

We will also control for a number of variables that could influence students’ MVPA during lessons. These include temperature at the start time of the lesson, the type of activity included in the lesson and the timing of accelerometer fitting for the lesson (the student arrived at lesson wearing an accelerometer or was fitted at started of lesson).

Generalized linear mixed models will be also used to examine mediation hypotheses. Mediating effects will be estimated using a cluster-bootstrapped based product-of-coefficients test that is appropriate for cluster randomized controlled trials [75].

Potential moderators of the intervention effects will also be explored. Potential moderators will include gender and ethnic background (categorical variables), as well as socio-economic status and baseline levels of physical activity and psychosocial variables (e.g., motivation and needs satisfaction) which will be treated as continuous variables. Moderator effects will be explored using the same generalized mixed modeling approach by including appropriate interaction terms in the regression models. The trial is powered to detect main effects, not interactions; thus, we will employ a less stringent significance level to explore potential moderators. Interaction terms that are significant at *p* < 0.1 will be explored by testing differences in intervention effects across sub-groups stratified according to the moderator variable [76].

Per protocol analyses will investigate the influence of teachers’ adoption of the intervention, as indicated by the proportion of intervention components completed by each teacher (e.g., workshops attended and online tasks completed), on student outcomes (e.g., MVPA during PE lessons). Analyses will also examine the effect of teachers’ implementation of the intervention, as indicated by increases in their use of AMPED teaching strategies from baseline to post-intervention (observed in video recordings of their lessons), on student outcomes.

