## Methods

### Design

The trial will take place in government-funded secondary schools in the Western Sydney region of Australia, one of the fastest growing areas in the nation. This region has a large proportion of youth who come from low socio-economic status (SES) and immigrant backgrounds [43, 44], meaning they are at greater risk of physical inactivity compared with the Australian average [45].

This will be a two-arm, cluster randomized controlled trial with allocation at the school level (1:1 ratio to intervention and control conditions). See CONSORT flow diagram (Fig. 2). School years in Australia run from the end of January to the middle of December, with a summer break from mid-December to late January. Assessments will be completed at baseline of the first year (Term 1, February-April) and post-intervention (Term 4, September-December 2014: 7–8 months after baseline), which is the primary endpoint for this trial. A maintenance phase assessment will be conducted 14–15 months after baseline (Term 2, May–July).

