### Sample size

Sample size calculations were based on estimated effect sizes for the primary outcome. A recent meta-analysis [3], indicated that lesson planning and delivery interventions have a pooled effect of *d* = 0.60 on MVPA during PE lessons. To ensure 80 % power to detect an effect of this size would require 90 participants in a non-clustered trial (two-tailed probability level of 0.05). We considered the clustered nature of the data, including both school and class levels [46]. However, results from recent studies of MVPA in PE lessons indicated that clustering at the school level was negligible after accounting from clustering at the class level [22, 33]. As a result, we adjusted our sample size calculations for clustering using the formula 1 + (*m*-1)ρ, where *m* is the number of students per class and ρ is the intra-class correlation (ICC) [46].

Our recent study in Sydney-area schools indicated a class-level ICC of 0.62 [22], which was similar to Aelterman et al. [33] who reported a class-level ICC of 0.63. With an estimated class size of 22 participating students, an adjustment of 14.23 was required: 1 + (22–1)*0.63 = 14.23. Multiplying by the 90 participants required in non-clustered trial, we estimated that 1280 students would need to participate to achieve 80 % power. We estimate that 14 schools, with a mean of 4.5 classes of Year 8 students per school can be recruited and, therefore, aim to recruit 1386 students (14 schools × 4.5 classes per school × 22 students per class). Potential loss to follow up of up to 30 % of participants (*n* = 384; a very conservative estimate) will not substantially impact on the statistical power of the study. This resilience to loss of power exists because this study will use generalized mixed models, enabling the inclusion of all participants (included at baseline) in the analyses. In non-clustered longitudinal clinical trials, this analytic approach has been shown to yield similar point estimates and smaller decreases in statistical power than multiple imputations [47, 48].

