### Recruitment and randomization

Principals and Head Teachers of PE from all secondary schools that meet our eligibility criteria will be invited to express their interest in participating in this study. From the schools that indicate an interest in the study, we will attempt to purposively select schools in order to ensure that the sample is representative of the region’s population, in terms of school size and gender composition (i.e., single sex or co-educational). Schools that agree to participate will be match paired according to SES of the postcode in which the school is located (according to the Index of Relative Socio-Economic Disadvantage:), school size (Year 8 enrolment), gender composition of PE classes (i.e., single sex vs co-ed) and the duration of PE lessons. Using a computer-based randomization plan generator, the 14 schools will be randomized to the control or intervention condition from within each pair following baseline assessments. A researcher not associated with recruitment or data collection, and who will be blind to school identity, will carry out randomization procedures.

All PE teachers in schools that enter the trial will be invited to an information session during which study procedures will be outlined and questions answered. The research team will present study information and provide an information letter and consent form to all Year 8 students from classes whose teacher agrees to participate.

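### The primary model leaves the baseline difference between arms free although schools are randomised after baseline; the estimate is unbiased but gives up precision that could be had at no cost

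*Protocol article*

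**What the plan says.** The Statistical analysis section of the Protocol article states the target as a contrast in change: "Between-arm differences in changes on the primary and secondary outcomes will be analyzed using generalized linear mixed models". The model does this "by including an indicator variable for group allocation (arm), a variable representing time (baseline, post-intervention, and/or maintenance) and their interaction".

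The random part is also given: "we will include four random intercept effects: (i) lesson; (ii) student; (iii) teacher; and (iv) class", with school added if preliminary analyses suggest clustering at that level. The adjustment variables for the primary outcome are listed separately: "These include temperature at the start time of the lesson, the type of activity included in the lesson and the timing of accelerometer fitting". Baseline MVPA is not among them. Baseline physical activity appears later in the same section, but only as a possible moderator.

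Under Recruitment and randomization, the order of events is clear: "the 14 schools will be randomized to the control or intervention condition from within each pair following baseline assessments". Under Design, the post-intervention assessment is the one "which is the primary endpoint for this trial".

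The Sample size section compares two means at a single time point and multiplies by a design effect. It uses no correlation between baseline and follow-up.

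**The concern.** Because baseline precedes allocation, any baseline difference between the arms is chance, and its expected value is zero. A model with a free arm main effect estimates that difference anyway and subtracts all of it from the follow-up difference. A model that takes the baseline means as equal subtracts only the part that predicts follow-up.

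At stake is precision on the primary outcome in a trial with 14 randomised schools. If class means correlate weakly between the two assessments, the planned contrast could even be less precise than ignoring baseline altogether, and the stated 80% power would not be reached. The model is written into the article, so this is a stated choice and not a detail left to an analysis plan that is not shown.

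**Working it through.** **Inputs from the Protocol article (Sample size):** d = 0.60 from "lesson planning and delivery interventions have a pooled effect of *d* = 0.60 on MVPA during PE lessons"; two-sided 0.05; 80% power; class-level ICC 0.63; 22 students per class; 14 schools with 4.5 classes each. **Assumed, because the article gives no value:** r, the correlation of class means between baseline and post-intervention.

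**Step 1. Reproduce the stated figures.** A t-based two-sample calculation gives 45 per arm, 90 in total (power 0.804). Design effect: 1 + 21 × 0.63 = 14.23. Required: 90 × 14.23 = 1280.7, stated as 1280. Target: 14 × 4.5 × 22 = 1386. All agree with the article.

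**Step 2. Variances relative to a follow-up-only comparison.**
- Planned contrast (free baseline difference): 2(1 − r).
- Baseline means constrained equal: 1 − r².
- Ratio: 2(1 − r)/(1 − r²) = 2/(1 + r), which exceeds 1 for every r below 1.
- The planned contrast matches the follow-up-only comparison when 2(1 − r) = 1, that is at r = 0.5.

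**Step 3. Power at 1386 students.** Effective N = 1386/14.23 = 97.4. With variance multiplier k, power by the normal approximation is Φ(0.6 × √(97.4/4)/√k − 1.96) = Φ(2.961/√k − 1.96). Follow-up only (k = 1): Φ(1.001) = 84%. Planned model at r = 0.2 (k = 1.6): Φ(2.341 − 1.96) = Φ(0.381) = 65%.

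| r (assumed) | k planned | k constrained | ratio | power planned | power constrained |
|---|---|---|---|---|---|
| 0.2 | 1.60 | 0.96 | 1.67 | 65% | 86% |
| 0.4 | 1.20 | 0.84 | 1.43 | 77% | 90% |
| 0.5 | 1.00 | 0.75 | 1.33 | 84% | 93% |
| 0.7 | 0.60 | 0.51 | 1.18 | 97% | 99% |
| 0.8 | 0.40 | 0.36 | 1.11 | 99.7% | 99.9% |

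**Step 4. Check with a repeated-measures structure.** Generalised least squares was applied to 63 classes (14 × 4.5) of 22 students, three lessons at each of two times, with class, lesson, student and residual components. The split was assumed: class plus lesson 0.63, student 0.20, residual 0.17. The share of the 0.63 that belongs to the class, and so is stable over time, was varied.

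| stable share | r | variance, arm term free | variance, arm term dropped | ratio |
|---|---|---|---|---|
| 10% | 0.27 | 0.02433 | 0.01549 | 1.57 |
| 25% | 0.51 | 0.02033 | 0.01535 | 1.33 |
| 50% | 0.75 | 0.01366 | 0.01196 | 1.14 |
| 90% | 0.96 | 0.00299 | 0.00293 | 1.02 |

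In each case the interaction variance with the arm term free equalled the variance of the difference in mean changes, and the ratio equalled 2/(1 + r). The equality is exact for balanced, complete data with an identity link. It is approximate here, since the article expects one to three lessons per student, changes of teacher and some loss to follow-up.

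**The case against.** The strongest defence is that arm, time and their interaction form a standard repeated-measures model that matches the stated aim and is valid. That stands. A reader might infer bias from regression to the mean. The article does not support this: over the randomisation the contrast is unbiased, and the concern applies only conditionally, when the arms happen to differ at baseline. Matching within pairs does not remove such imbalance, because MVPA is not among the matching variables.

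A second defence is that r may well be high. Up to three lessons are averaged per assessment, the model adjusts for activity type and temperature, and in Step 4 r falls below 0.5 only when less than about a quarter of the class and lesson variance is stable. This also stands, as far as assumed variance shares can carry it. Against it, teachers may change, some students contribute a single lesson, and baseline and endpoint fall in different school terms. The article does not settle the value.

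A reader might also calculate power with 12 degrees of freedom for 14 schools, obtain 78% for the planned model at r = 0.5, and blame the change contrast. That would be wrong: at r = 0.5 the contrast is exactly as precise as the follow-up-only comparison, and the article's own method gives 84%. Degrees of freedom are a separate question.

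**Conclusion.** The point holds as one of efficiency, not validity. The planned model is less precise than the constrained one at every r below 1, by about 67% extra variance at r = 0.2, 33% at 0.5 and 11% at 0.8.

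It would be tempting to conclude that the trial is underpowered. The article does not support that. The planned analysis falls short of the precision assumed in the sample size only if r is below 0.5. At r = 0.7 it has about 97% power, well above target.

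These figures rest on an assumed r, the article's design effect with no school-level clustering, a normal approximation and near-balanced data. The advantage of the constrained model is a large-sample result, to be read with some caution with 14 randomised schools. The change is still worth making, because it uses baseline data the trial already collects.

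**What to change.** In the Statistical analysis section, keep baseline as an outcome row but remove the arm main effect. The fixed part then has time and arm by post-baseline time, with baseline means constrained equal across arms. Keep the same random effects and lesson covariates. Use the same form for secondary outcomes measured at baseline.

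This keeps every student with a baseline assessment, as the article's intention-to-treat definition requires. Post-intervention MVPA regressed on student and class baseline MVPA can serve as a sensitivity analysis. It should not be called equivalent, because it drops students without a follow-up value, and the Sample size section allows for up to 30% loss.

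The cost is a change of model wording. No extra data, visits or participants are needed.

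### The primary arm-by-time test has no class-by-time or school-by-time random effect, so its standard error is too small if such variation remains after the teacher effect and covariates

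*Protocol article*

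**What the plan says.** All of this is in the protocol article. Under Design, the trial is a "cluster randomized controlled trial with allocation at the school level (1:1 ratio to intervention and control conditions"; the primary endpoint is the post-intervention wave, 7–8 months after baseline. Under Primary outcome, MVPA is measured in three PE lessons per wave.

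Under Statistical analysis, arm differences in change are assessed "by including an indicator variable for group allocation (arm), a variable representing time (baseline, post-intervention, and/or maintenance) and their interaction". The random part for the primary outcome is then summarised: "In sum, we will include four random intercept effects: (i) lesson; (ii) student; (iii) teacher; and (iv) class". One addition is left open: "We will consider a fifth random intercept effect for school, if preliminary analyses suggest clustering of MVPA during lessons at the school level". Teacher effects are cross-classified, because "In some instances students will be taught by different teachers within a time point (i.e., from lesson to lesson) or across time points". The model also adjusts for temperature at the start of the lesson, type of activity and timing of accelerometer fitting.

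No random time slope, class-by-time term or school-by-time term is named.

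**The concern.** The quantity tested is a difference between arms in change. A class, student or school intercept takes the same value at baseline and at follow-up, so it largely drops out of a change. What mainly remains as error is lesson-to-lesson variance, and the three lessons of a class within a wave count as three independent observations once the class is given.

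Those lessons share whatever has moved the class since baseline. Baseline falls in Term 1 and the primary endpoint in Term 4, so a class or a whole school can shift between them for reasons unrelated to the intervention. Because schools are randomised, the variation in change between schools, and between classes within schools, is the error against which the arm-by-time effect should be judged.

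The conditional school intercept does not supply that error. It is constant over time and cancels as well. The condition for adding it concerns school clustering of MVPA during lessons, which is not clustering of change. The Sample size section's evidence that school clustering is negligible after class is also evidence about MVPA in lessons.

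At stake are the primary p-value and confidence interval, which could be too favourable in either direction of effect.

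**Working it through.** **Inputs.** From Sample size: 14 schools, 4.5 classes per school, 22 students per class, two-sided 5% level. From Primary outcome: 3 lessons per class per wave. Two waves are used (baseline and the primary endpoint).

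**The plan's own figures reproduce.** 1 + (22 − 1) × 0.63 = 14.23; 90 × 14.23 = 1280.7, stated as 1280; 14 × 4.5 × 22 = 1386. The point here concerns the analysis model, not this arithmetic. The number of classes is 14 × 4.5 = 63.

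**Assumptions.** Balanced lesson means, no true effect, normal critical value 1.96, class and lesson terms only. Teacher effects, covariates and dropout are left out. Lesson variance is set to 1, class-by-time variance is *a* and school-by-time variance is *b*. The article gives neither *a* nor *b*.

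**Step 1: degrees of freedom within class.** Lesson means: 63 × 2 × 3 = 378. Removing 63 classes, time and arm-by-time leaves 378 − 65 = 313. Of these, 63 − 2 = 61 are class-by-time and 63 × 2 × 2 = 252 are between lessons in the same class and wave.

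**Step 2: variance the contrast needs**, on the scale of a single lesson mean: 1 + 3*a* + 3 × 4.5 × *b* = 1 + 3*a* + 13.5*b*.

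**Step 3: variance the listed terms supply.** A model with class and lesson intercepts pools all 313 degrees of freedom: 1 + (61/313) × [3*a* + 3*b* × (63 − 9)/61] = 1 + 0.585*a* + 0.518*b*. The lesson term therefore picks up about one fifth of the class-by-time part (61/313 = 0.195), and less of the school-by-time part (0.518/13.5 = 0.04).

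**Step 4: ratio and type I error.** Ratio of model to true standard error *r* = √(Step 3 / Step 2); type I error = 2 × [1 − Φ(1.96 *r*)].

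| *a* | *b* | needed | supplied | *r* | type I error |
|---|---|---|---|---|---|
| 0 | 0 | 1.000 | 1.000 | 1.00 | 5.0% |
| 0.10 | 0 | 1.300 | 1.058 | 0.90 | 7.7% |
| 0.25 | 0 | 1.750 | 1.146 | 0.81 | 11.3% |
| 0.50 | 0 | 2.500 | 1.292 | 0.72 | 15.9% |
| 0 | 0.05 | 1.675 | 1.026 | 0.78 | 12.5% |
| 0.25 | 0.05 | 2.425 | 1.172 | 0.70 | 17.3% |

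**Check by simulation.** A mixed model with a class intercept was fitted by REML to simulated lesson means, 400 runs per setting. Variances were set as shares of the 0.63 class-level variance, with lessons taking 30%. With no time-varying cluster variance, type I error was 4.8%. With class-by-time variance at 10% of the class-level variance it was 11.0% (formula 12.5%), and at 20% it was 16.3% (formula 17.6%). At this number of runs the standard error of an 11% rate is √(0.11 × 0.89/400) = 1.6 percentage points, so the two agree.

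**The alternative.** A t-test on the 14 school mean changes (14 − 2 = 12 degrees of freedom, pairing ignored) gave 4.8% to 5.0% over 20,000 simulated trials in each of four settings: (*a*, *b*) = (0, 0), (0.25, 0), (0, 0.05) and (0.25, 0.05).

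**The case against.** The strongest reply is that much wave-to-wave variation is already modelled. Activity type is a covariate in nine categories. Temperature is a direct, though partial, proxy for season. Fitting time is adjusted for. Where a class's teacher changes between waves, the cross-classified teacher effect does not cancel and enters the error of the contrast. The lesson term also takes up a minor share. All of this stands, and it means the class-plus-lesson model probably overstates the inflation. It does not remove the gap: apart from what the measured covariates explain, no listed term covers a school-wide shift, or a shift in a class that keeps its teacher.

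A reader might infer that the primary standard error is certainly too small, or that cluster-by-time variation is ignored altogether. The article supports neither. The first holds only if residual cluster-by-time variance is above zero, and no value is given; the second overlooks the terms just named. A reader might also carry the formula to *a* = 1.0 and quote 22% as the error rate. Nothing in the article supports class-by-time variance as large as lesson variance after adjustment for activity and temperature.

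The sentence on modelling the repeated measure as a random intercept could be read as a time-specific term. The closing list resolves it to a student intercept. Even a student-by-time effect, independent between classmates, would not carry a shift that they share.

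Finally, two further variance components with 14 schools may be estimated at zero. That is a real cost, and the reason to name a fallback.

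**Conclusion.** The concern holds conditionally. The listed random effects contain no term for class-level or school-level change, although change is what is tested and schools are what is randomised. If residual class-by-time or school-by-time variance remains after the teacher effect and covariates, the primary test is anti-conservative, and the optional school intercept does not cure it.

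The size is illustrative only: about 8% to 16% type I error for class-by-time variance of 0.10 to 0.50 of lesson variance, and about 12% for school-by-time variance of 0.05 alone. These figures rest on assumed ratios, balanced data, and a model without teacher or covariate terms. With no such variance the error rate is the nominal 5%. The point still deserves correction before analysis, because it bears on the primary standard error and the remedy is cheap.

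**What to change.** Add random class-by-time and school-by-time effects to the primary arm-by-time model, alongside the effects already listed. Use small-sample degrees of freedom that reflect the 14 schools. State that these terms are included by design and do not depend on a preliminary test.

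Name a fallback in advance: if the fit is singular or does not converge, the primary inference comes from a school-level analysis of change on about 12 degrees of freedom. Otherwise report that analysis as confirmation.

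The cost is a change of analysis wording, a larger model, somewhat wider intervals and possible boundary estimates of the new components. No new data are needed.
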